##### PARTICIPANT EXCLUSION CRITERIA:

1. Pregnancy as determined by a positive urine beta-hCG (if female).
2. Participant unwilling to use reliable contraception methods for the duration of the trial. Reliable methods of birth control include: pharmacologic contraceptives including oral, parenteral, and transcutaneous delivery; condoms with spermicide; diaphragm with spermicide; surgical sterilization; vaginal ring; intrauterine device; abstinence; and post-menopause (if female).
3. Currently breast-feeding (if female).
4. Latest CD4 count < 200 x106 cells/µL
5. Viral load (HIV RNA) > 50 copies/mL **if** on HAART (defined as at least three antiretrovirals including either a protease inhibitor or a NNRTI, i.e. combivir 300/150 mg x2 + stocrin 600 mg x1 for a minimum of 6 months)
6. Previous enrollment in this study.
7. Any medical, psychiatric, social, or occupational condition or other responsibility that, in the judgment of the Principal Investigator (PI), would interfere with the evaluation of study objectives (such as severe alcohol abuse, severe drug abuse, dementia).
8. Unable to follow protocol regimen
9. Pneumococcal vaccination 5 years or less prior to inclusion
10. Planned participation in other vaccination trials during the time of the study

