**PRIMARY ENDPOINTS:**

*At six months after 2nd vaccination with Prevenar.*

- Pneumococcal vaccine high responders defined as 2-fold increase and IgG levels ≥1 µg/mL to at least 5 of 7 pneumococcal serotypes (by quantitative IgG measurements)

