**Primary endpoint**

Prevalence ratios of high responders at six months after 2nd vaccination with Prevenar, comparing the two vaccination scheme groups (with/without CPG 7909), will be estimated by Poisson regression adjusted by age, CD4 cell count at baseline and HAART (on HAART vs. no HAART) at baseline.

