# SCHEDULE OF ASSESSMENTS/PROCEDURES

| **Assessments/ Procedures** | **Baseline** | **Vaccination** | | | **Follow-up** | | | |
| --- | --- | --- | --- | --- | --- | --- | --- | --- |
| **Study Day** | **Predose** | **Day 0 (1)** | **Day 90 ± 14 (2)** | **Day 270 ± 30 (2)** | **Day 90 ± 14 (3)** | **Day 270 ± 30 (4)** | **Day 300 ± 30 (4)** | |
| Written Informed Consent | X |  |  |  |  |  |  | |
| Inclusion/Exclusion Criteria | **X** |  |  |  |  |  |  | |
| Medical History and Demographics | **X** |  |  |  |  |  |  | |
| Pregnancy Test**(5)** | **X** |  | **X** | **X** |  |  |  | |
| Randomization | **X** |  |  |  |  |  |  | |
| Conjugate pneumococcal vaccine ± CPG 7909 **(6)** |  | **X** | **X** |  |  |  |  | |
| Polysaccharide pneumococcal vaccine ± CPG 7909 **(6)** |  |  |  | **X** |  |  |  |  |
| **Safety** |  |  |  |  |  |  |  | |
| Physical Examination |  | **X(7)** | **X(7)** | **X(7)** | **X(8)** | **X(8)** | **X(8)** | |
| Bloodpressure and Heartrate |  | **X(7)** | **X(7)** | **X(7)** | **X** | **X** | **X** | |
| Lab Safety Tests**(9, 10)** | **X** |  |  |  | **X** | **X** | **X** | |
| HIV Control Parameters**(11)** | **X** |  |  |  | **X** | **X** | **X** | |
| Adverse Events**(12)** |  | **X** | **X** | **X** | **X** | **X** | **X** | |
| **Efficacy** |  |  |  |  |  |  |  | |
| Functional antibody response | **X** |  |  |  | **X** | X | X | |
| Quantitative antibody response | **X** |  |  |  | **X** | **X** | **X** | |
| Oropharyngeal swap | **X** |  |  |  |  | **X** | **X** | |
| Immunologic markers **(13)** | **X** |  |  |  | **X** | **X** | **X** | |

1. Day 0 vaccination is conducted after all baseline assessments/procedures are made.
2. Day 90 follow-up and vaccination can vary by 14 days
3. Follow-up is done before proceeding to 2nd vaccination
4. Follow-up day 270 and day 300 is allowed to vary by 30 days.
5. Women of childbearing potential only.
6. According to randomization.
7. Participants asked to stay in for at least ½ hour post-vaccination. A physical examination incl. BP and HR will be made before discharge.
8. Physical examination will be made on participants request or if the investigator finds it relevant.
9. Complete bloodcount, serum chemistry and liver parameters
10. If a participant withdraws prematurely, lab safety tests must be done within approximately one week of participant withdrawal
11. Viral load (HIV RNA) and CD4-count

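### The primary model omits baseline IgG, which is measured before the first dose and is a term in the 2-fold criterion; adding it, with robust variance, would protect against chance imbalance at almost no cost

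*Protocol*

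**What the plan says.** Under Statistical Analyses, Primary endpoint, the protocol says that the prevalence ratio of high responders is to come from a Poisson regression "adjusted by age, CD4 cell count at baseline and HAART (on HAART vs. no HAART) at baseline". That list is closed, and no section names baseline IgG as a covariate for any analysis.

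The endpoint (Primary Endpoints) is "Pneumococcal vaccine high responders defined as 2-fold increase and IgG levels ≥1 µg/mL to at least 5 of 7 pneumococcal serotypes", assessed "At six months after 2nd vaccination with Prevenar", which is day 270.

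The Schedule of Assessments has a row "Quantitative antibody response" marked at predose and at the day 90, 270 and 300 follow-ups. The Procedures section confirms that baseline blood is taken before immunisation. Earlier pneumococcal vaccination excludes a person only if it was recent: "Pneumococcal vaccination 5 years or less prior to inclusion".

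The Randomization section balances the arms on HAART status only. Baseline differences between arms are to be tested (Baseline characteristics).

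**The concern.** A rise is always measured from somewhere. For each serotype the starting IgG sets the level that counts as a doubling, so a high start makes the fold criterion harder to meet. A high start may also go with a higher level at day 270, which makes the 1 µg/mL criterion easier. Either way, baseline IgG is a plausible predictor of the outcome, is already collected, and is absent from a model that the protocol itself fixes.

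With about 42 evaluable participants per arm, a chance difference in baseline IgG could shift the responder proportions and be offered as an alternative explanation of the result. If the planned baseline tests showed such a difference, adding the covariate then would be a data-driven change to the primary analysis. Leaving it out would leave the doubt standing. Naming it in advance avoids both.

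**Working it through.** **1. The plan's own figure.** Inputs from Estimated Sample Size: 30% versus 60%, two-sided α 0.05, power 0.80, 10% drop-out. With pooled variance and no continuity correction:

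n = [1.960·√(2·0.45·0.55) + 0.842·√(0.3·0.7 + 0.6·0.4)]² / 0.30² = (1.379 + 0.565)² / 0.09 ≈ 42 per group.

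42/0.9 = 46.7, so 47 per group and 94 in total. All 25 cells of the protocol's table reproduce in the same way. No covariate enters this calculation, so N does not depend on the point made here.

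**2. Where baseline enters the endpoint.** A serotype counts when day-270 IgG ≥ max(2 × baseline, 1 µg/mL). Baseline is an arithmetic term in the first criterion only. It can affect the second only through its correlation with the post-vaccination level. The two influences pull in opposite directions.

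**3. How large a chance imbalance is ordinary.** The standardised difference in baseline means between arms has SD √(2/42) = 0.218, so its 95% range is ±1.96 × 0.218 = ±0.43 SD.

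**4. Why the variance estimator matters.** Expected responders are 42 × 0.3 = 12.6 and 42 × 0.6 = 25.2. For log(2) = 0.693:

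- Model-based Poisson SE: √(1/12.6 + 1/25.2) = 0.345, so z = 2.01 and power is about 0.52.
- Robust SE: √(0.7/12.6 + 0.4/25.2) = 0.267, so z = 2.59 and power is about 0.74.

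**5. Effect of adding the covariate.** The protocol gives no IgG distribution, so these inputs are assumptions: baseline mean 0.5, 1 or 2 µg/mL; SD 1.5 on the log2 scale; slope of log2 rise on log2 baseline 0, −0.3 or −0.6; between-serotype correlation 0.5; residual SD 1.2. Each scenario was calibrated to 30% versus 60%, with 2,000 trials of 42 per arm. The comparison is treatment alone against treatment plus mean log2 baseline IgG over the seven serotypes.

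| Baseline mean, slope | Control response by baseline tertile | Robust power, without → with | Model-based power, without → with |
|---|---|---|---|
| 0.5, 0 | 0.10 / 0.34 / 0.46 | 0.769 → 0.830 | 0.538 → 0.525 |
| 0.5, −0.3 | 0.18 / 0.37 / 0.35 | 0.757 → 0.778 | 0.538 → 0.524 |
| 0.5, −0.6 | 0.30 / 0.37 / 0.23 | 0.773 → 0.788 | 0.544 → 0.537 |
| 1, 0 | 0.19 / 0.35 / 0.37 | 0.764 → 0.794 | 0.526 → 0.522 |
| 1, −0.3 | 0.30 / 0.35 / 0.24 | 0.768 → 0.778 | 0.535 → 0.526 |
| 1, −0.6 | 0.43 / 0.33 / 0.14 | 0.746 → 0.802 | 0.524 → 0.526 |
| 2, 0 | 0.26 / 0.32 / 0.32 | 0.768 → 0.786 | 0.544 → 0.534 |
| 2, −0.3 | 0.39 / 0.32 / 0.20 | 0.788 → 0.818 | 0.566 → 0.556 |
| 2, −0.6 | 0.52 / 0.29 / 0.10 | 0.758 → 0.839 | 0.542 → 0.542 |

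With robust variance the gain runs from 1.0 point (0.768 → 0.778) to 8.1 points (0.758 → 0.839). With model-based variance the change runs from −1.4 to +0.2 points. The median prevalence ratio stays at 2.00 to 2.04 with and without the covariate, as randomisation implies. Monte Carlo error is about √(0.77·0.23/2000) = 0.9 points per power estimate.

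A second set of nine scenarios (1,500 trials each, baseline log10 SD 0.45) gave robust power of 75–79% without and 78–85% with the covariate, a gain of 1 to 6.5 points. Its variance ratio was 0.91 to 1.015.

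**6. Effect of an imbalance in one trial.** Under the assumptions of step 5, with arms differing by −0.43 or +0.43 SD, a true ratio of 2.0 averages about 1.66 or 2.41 unadjusted in one scenario, and about 2.45 or 1.64 in another. In the flattest scenarios it stays within 1.95 to 2.05. With the covariate it stays close to 2.0 throughout (1.96 to 2.05 in that run).

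**The case against.** The strongest reply is that nothing here is an error. The protocol prespecifies a complete covariate set, treatment is randomised, and the sample size reproduces exactly. A reader might infer from the omission that the primary comparison is biased or the trial underpowered. The documents support neither: the comparison is unbiased over repeated randomisations, and N was derived without any covariate. That stands, and it limits the point to precision and to chance imbalance in this one trial.

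Two further inferences fail. One is that baseline IgG is built into both halves of the endpoint; it is a term in the doubling criterion only. The other is that the listed covariates are weaker predictors. The protocol reports no predictor's strength, and it gives reasons for its choices: HAART is balanced at randomisation, and CD4 is discussed as relevant to vaccine benefit.

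The size is also open to challenge. Every distributional input is assumed, and the direction of the baseline effect changes across scenarios. The comparator in step 5 was treatment alone, so the gain over a model already containing age, CD4 and HAART is not shown. A single linear term cannot capture a non-monotone relation such as 0.30/0.35/0.24, although in such scenarios there is little to adjust for. All of this stands. The enrolment of people vaccinated more than five years earlier is weak evidence of spread in baseline IgG, because the Background says that polysaccharide-induced antibody in such patients is short-lived.

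One might also fault the secondary analyses for leaving their covariates unnamed. Such detail is commonly left to a statistical analysis plan, so it is not raised here.

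What the reply does not remove is the single-trial problem. Randomisation protects on average, and only HAART is balanced by design.

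**Conclusion.** The point holds as a modest improvement to a choice that the protocol itself fixes. Baseline IgG is measured before dose 1, is a term in the fold criterion by construction, and is missing from the primary model. The omission leaves chance imbalance unadjusted and may lose some precision.

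Under the assumed IgG distributions the power gain is about 1 to 8 points with robust variance. It is close to zero where the two influences of baseline offset, and absent with model-based Poisson variance. All power runs were made under the alternative, so a gain of a point or two should not be over-read. The case for the change rests more on ruling out an avoidable alternative explanation in advance than on power.

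**What to change.** In Statistical Analyses, Primary endpoint, add to age, baseline CD4 count and baseline HAART status one further prespecified covariate: the participant's mean of log baseline IgG over the seven serotypes. State in the same sentence that standard errors and confidence intervals use robust (sandwich) variance; without that, no power gain should be expected.

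The cost is one coefficient. With 12.6 + 25.2 = 37.8 expected responders, the model goes from four coefficients besides the intercept (9.5 responders each) to five (7.6 each). No extra samples, visits or participants are needed, and N stays at 94. A missing baseline sample adds little difficulty, because such a participant cannot be scored on the doubling criterion in any case.

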**Secondary endpoints**

Comparison of endpoints between the study groups will be done by Poisson regression (dichotomous endpoints) or linear regression (continuous endpoints), adjusted for appropriate potential confounders.

Predictors for achieving a high vaccination response (classified as a high responder) at six months after 2nd vaccination with Prevenar will be estimated by multivariate Poisson regression.

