##### PROCEDURES:

Consenting participants that pass the inclusion/exclusion criteria will be enrolled in the study. Blood samples for baseline parameter measurements will be drawn before proceeding to immunization.

At randomization, participants will be allocated 1:1 one of two study regimens:

- **Experimental group**: Double paediatric dose of 7-valent conjugate pneumococcal vaccination (Prevenar®, Wyeth) + 1 mg CPG 7909 (day 0), double paediatric dose of 7-valent conjugate pneumococcal vaccination (Prevenar®, Wyeth) + 1 mg CPG 7909 (day 90) and single dose of 23-valent polysaccharide vaccine (Pneumo Novum®, Sanofi Pasteur MSD) + 1 mg CPG 7909 (day 270)
- **Control group**: Double paediatric dose of 7-valent conjugate pneumococcal vaccination (Prevenar®, Wyeth) + 100 μl of placebo (day 0), double pediatric dose of 7-valent conjugate pneumococcal vaccination (Prevenar®, Wyeth) + 100 μl of placebo (day 90) and single dose of 23-valent polysaccharide vaccine (Pneumo Novum®, Sanofi Pasteur MSD) + 100 μl of placebo (day 270).

Blood samples are drawn and follow-up by the physician includes physical examination and medical history, registration of AEs/SAEs, vaccination history outside the study and any other information that may be relevant to document in the CRF. A concluding visit is scheduled at day 300.

A subject who returns for the concluding visit or is available for the concluding contact foreseen in this protocol is considered to have completed the study.

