##### SECONDARY EFFICACY PARAMETER AND ANALYSIS OF ANTIBODY RESPONSE

Measuring the quantitative amount of serotype specific anticapsular antibodies does not give any information the functionality of the antibodies. This can be measured by a flow-cytometric opsonophagocytic assay and gives indirect information on the antibodies ability to opsonize and facilitate killing of invading pneumococci{{75 Martinez,J.E. 2006; }}. The result of a recent WHO seminar held in January 2007 on standardization of opsonophagocytic assays is expected to be published soon and any possible changes to the method described below will be incorporated.

*Qualitative* analysis are done using a flowcytometric opsonophagocytic assay which measures functional (opsonophagocytic) activity (OPA) of the serotype specific antibodies. In short: Eight twofold dilutions are made in OPA buffer from 10 μl of test serum. A 20-μl aliquot of either multiplex bacteria or multiplex bead suspension containing 1x105 of each of the target pneumococcal serotype or pneumococcal polysaccharide-conjugated beads is added to each

well, and the plate is incubated for one hour at 37°C with horizontal shaking (200 rpm). Following this, 20 μl of sterile serum from 3- to 4-week-old baby rabbit serum (Pel-Freez, Brown Deer, Wis.) is added to each well except for HL60 cell control wells, which receives 20 μl of OPA buffer. After incubation at 37°C for 20 min with shaking (200 rpm on an orbital shaker), 30 μl of washed HL60 polymorphonuclear leukocytes (PMNs) (2.5 μ 104/ml) are added to each well, resulting in an effector-to-target ratio of 1:4 (for each target type). The final well volume is 80 μl, with the first well of a dilution series containing a 1:8 final dilution. The plate is then incubated for 60 min with shaking at 37°C. An additional 80 μl of OPA buffer is added to every well to provide sufficient volume for flow cytometric analysis and the well contents transferred to microtiter tubes (Bio-Rad, Hercules, Calif.). Up to 12 serum samples can be assayed per plate, including a quality control sample. Flow analysis are done by Flow Applications, Inc, Ill, USA{{75 Martinez,J.E. 2006; }}.

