**SECONDARY ENDPOINTS:**

**IMMUNOGENICITY**

*At three months after 1st vaccination with Prevenar.*

- Pneumococcal vaccine high responders defined as 2-fold increase and IgG levels ≥1 µg/mL to at least 5 of 7 pneumococcal serotypes (by quantitative IgG measurements)
- Opsonophagocytic activity for serotypes 6B, 14, 19F and 23F expressed as titers
- Serotype-specific antibody response defined as 2-fold increase and IgG levels ≥1 µg/mL
- Serotype-specific antibody response defined as change in IgG levels

*At six months after 2nd vaccination with Prevenar.*

- Opsonophagocytic activity for serotypes 6B, 14, 19F and 23F expressed as titers
- Serotype-specific antibody response defined as 2-fold increase and IgG levels ≥1 µg/mL
- Serotype-specific antibody response defined as change in IgG levels
- Cellular immune response

*At one month after vaccination with Pneumo Novum.*

- Pneumococcal vaccine high responders defined as 2-fold increase and IgG levels ≥1 µg/mL to at least 5 of 7 pneumococcal serotypes (by quantitative IgG measurements)
- Opsonophagocytic activity for serotypes 6B, 14, 19F and 23F expressed as titers
- Serotype-specific antibody response defined as 2-fold increase and IgG levels ≥1 µg/mL
- Serotype-specific antibody response defined as change in IgG levels
- Geometric Mean Antibody Concentrations With the Standard Enzyme Immunoassay for serotypes 1, 4, 7F, 9V, 14, 18C and 19F

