##### ESTIMATED SAMPLE SIZE

**Intention-to-treat (ITT) population:** all randomized participants

Sample size is calculated for the primary endpoint (prevalence ratios of **high responders at six months after 2nd vaccination with Prevenar**, comparing the two vaccination scheme groups). Setting the probabilities of Type I and Type II error to:

- Type I error probability (a) = 0.05 (two-sided).
- Type II error probability (ß) = 0.20 (power = 1 - ß = 0.80).
- Primary endpoint: proportion of vaccine highresponders (defined as2-fold increase and IgG levels ≥1 µg/mL to at least 5 of 7 pneumococcal serotypes).
- N is the number of participants needed in each group.

| Control\CpG | 0.50 | 0.55 | 0.60 | 0.65 | 0.70 |
| --- | --- | --- | --- | --- | --- |
| 0.20 | 39 | 29 | 23 | 18 | 15 |
| 0.25 | 58 | 41 | 31 | 24 | 19 |
| 0.30 | 93 | 61 | **42** | 31 | 24 |
| 0.35 | 170 | 96 | 62 | 43 | 31 |
| 0.40 | 388 | 173 | 97 | 62 | 42 |

Assuming a prevalence of 30% in control vaccine the group and a prevalence of 60% in the experimental vaccine group a sample size of 42 patients per group is required to detect a difference in prevalence estimated by Poisson regression. The expected drop-out percentage is set to 10%. Thus, a total of 94 subjects are needed in the study.

In accordance with the approach recommended by regulatory authorities, the two-sided 95% confidence interval (CI) of the immune response difference will be calculated.

Should the targeted number of participants not be reached within 12 months from study initiation the primary investigator can decide to stop the study if he considers reaching the expected 94 patients unlikely under the given circumstances. In that case all statistical analysis will then be based on the number of patients included at the time of study termination.

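### Linear regression is set for IgG change and OPA titres with no log scale and no baseline antibody term named; log-scale ANCOVA on data already collected would be more powerful

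*Protocol*

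**What the plan says.** The Secondary endpoints paragraph under Statistical Analyses assigns Poisson regression to dichotomous endpoints and, for the rest, "linear regression (continuous endpoints), adjusted for appropriate potential confounders". The adjustment phrase covers both kinds of model.

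The Immunogenicity list defines the continuous endpoints at three time points (three months after the first Prevenar dose, six months after the second, one month after Pneumo Novum):

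- "Serotype-specific antibody response defined as change in IgG levels"
- "Opsonophagocytic activity for serotypes 6B, 14, 19F and 23F expressed as titers"

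At the last time point it adds "Geometric Mean Antibody Concentrations With the Standard Enzyme Immunoassay for serotypes 1, 4, 7F, 9V, 14, 18C and 19F".

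The assay description explains where the OPA titres come from: "Eight twofold dilutions are made in OPA buffer from 10 μl of test serum", with the first well at a final dilution of 1:8.

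Baseline values will exist. Procedures states "Blood samples for baseline parameter measurements will be drawn before proceeding to immunization", and the Schedule of Assessments marks both the quantitative and the functional antibody response predose. Named covariates appear only for the primary endpoint, which is "adjusted by age, CD4 cell count at baseline and HAART (on HAART vs. no HAART) at baseline".

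**The concern.** Antibody concentrations are usually right-skewed, and vaccine effects on them are usually multiplicative. OPA titres rise by doublings by construction. The protocol itself thinks in these terms elsewhere, with a twofold-rise responder rule and a geometric mean endpoint. Yet the two main continuous endpoints are described as a change and as a titre, and are passed to linear regression with no mention of logs. Taken at face value, the treatment effect is a difference in arithmetic means, to which a few very high responders contribute most.

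The baseline antibody value is also unnamed as a covariate. A change score uses baseline, but less efficiently than adjusting for it. The OPA endpoint is a titre and not a change, so baseline OPA would not enter at all unless added.

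At stake are the power and readability of the continuous secondary immunogenicity results at days 90, 270 and 300. A geometric mean ratio can be read beside the twofold rule; an arithmetic difference cannot.

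**Working it through.** **The plan's own figure.** No sample size or power is given for the continuous endpoints. The only figure is for the binary primary endpoint ("Type I error probability (a) = 0.05 (two-sided", power 0.80, 30% versus 60%):

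n = [1.96·√(2·0.45·0.55) + 0.8416·√(0.30·0.70 + 0.60·0.40)]² / 0.30² = (1.379 + 0.565)² / 0.09 ≈ 42 per group.

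With 10% dropout, 42/0.9 = 46.7, so 47 per group and 94 in total. This reproduces the protocol and does not depend on the present point.

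**The OPA ladder, which needs no assumed SD.** Eight twofold dilutions from 1:8 give titres 8, 16, …, 8·2⁷ = 1024. The lowest step (8 to 16) is 8 units and the highest (512 to 1024) is 512 units. On the untransformed scale the same doubling therefore counts 512/8 = 64 times as much at the top. On log2 every step counts one.

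**Log-scale power for IgG, by formula.** Assumptions: n = 42 per group, ln-SD σ, baseline correlation ρ = 0.5, true ratio 1.75, so the effect is ln 1.75 = 0.560. Power ≈ Φ(0.560/SE − 1.96).

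- Log change: SE = σ·√[2(1−ρ)]·√(2/42) = 0.218σ
- Log value adjusted for log baseline: SE = σ·√(1−ρ²)·√(2/42) = 0.189σ

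At σ = 1.0 these give Φ(2.56 − 1.96) = 73% and Φ(2.96 − 1.96) = 84%.

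**Untransformed power, by simulation.** A difference of log-normal values has no equally simple formula. Under the same assumptions:

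| ln-SD | Raw change, no covariate | Log value adjusted for log baseline |
|---|---|---|
| 0.8 | 84% | 95% |
| 1.0 | 59% | 84% |
| 1.2 | 38% | 68% |

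A repeat run, with a threefold rise in controls assumed, agreed to within about two points.

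**Sensitivity.** With a true ratio of 2 and correlations from 0.3 to 0.7:

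| ln-SD | Raw change | Log value adjusted for log baseline |
|---|---|---|
| 0.7 | 0.98–0.99 | 1.00 |
| 1.0 | 0.74–0.82 | 0.91–0.99 |
| 1.3 | 0.41–0.50 | 0.72–0.92 |

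At ln-SD 1.0 and correlation 0.5, adding the raw baseline to the raw change moves power only from 0.77 to 0.78. Taking logs gives 0.87, and logs plus baseline 0.94. Most of the gain needs the log scale.

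**OPA.** On the 8-to-1024 ladder (ratio 1.75, correlation 0.5), power was about 50% for untransformed titres and about 79% for log2 titre adjusted for log2 baseline. These figures shift by several points with the assumed spread and with where typical titres sit on the ladder.

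**Type I error.** With no treatment effect, the raw IgG analysis rejected in 3.4% to 4.9% of runs in the sensitivity grid. It is not inflated.

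**The case against.** The strongest objection is that the protocol is silent here rather than wrong. A reader might infer that it orders an untransformed analysis and rules out a baseline term. It does neither. Regressing log IgG on treatment and log baseline is still linear regression with adjustment, and complies with the present text. The geometric mean endpoint and the twofold rule even suggest that the authors think multiplicatively. Transformations and covariate lists are often left to a SAP, which may exist. All of this stands. The point is therefore a better method at no cost, not a stated error.

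A reader might also infer three further things that the material does not support:

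- **Unreliable confidence intervals.** No coverage was calculated, and the type I error held.
- **Covariates chosen after seeing the data.** Leaving secondary covariates unnamed is ordinary SAP-level detail, and a SAP may fix them.
- **Deleting the confounder phrase as the remedy.** The phrase also governs the Poisson models for dichotomous secondary endpoints, which would then have no stated adjustment.

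Finally, the loss arises only if the analysis is really run untransformed, and at ln-SD 0.7 with a ratio of 2 it is negligible. These endpoints are secondary and stand beside responder endpoints at the same visits. What remains is that the protocol fixes the regression method and the endpoint definitions without the two features that make that method efficient for antibody data.

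**Conclusion.** The point holds as an improvement to the stated analysis. The protocol assigns linear regression to IgG change and OPA titres and names neither a log scale nor the baseline antibody value, although baseline is measured in everyone. If followed literally, power is lower than it need be by about 11, 25 and 30 percentage points at ln-SD 0.8, 1.0 and 1.2 (95 − 84, 84 − 59 and 68 − 38). This rests on assumed log-normal data with 42 per group, a ratio of 1.75 and a correlation of 0.5; the protocol supplies none of the last three quantities (SD, ratio, correlation). The loss is smaller with less spread and larger with more. Type I error, the primary endpoint and the sample size of 94 are unaffected.

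**What to change.** In the Secondary endpoints paragraph of Statistical Analyses:

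1. State that log IgG and log2 OPA titre at each visit are analysed by linear regression on treatment, the log baseline value of the same serotype, age, baseline CD4 count and HAART at baseline, and reported as geometric mean ratios with 95% CI.
2. For the dichotomous secondary endpoints, replace the general reference to confounders with the primary-model covariates (age, CD4 count, HAART). Do not simply delete it.
3. For the serotypes in the geometric mean endpoint after Pneumo Novum, use the same log scale, and add the baseline term wherever a baseline value for that serotype is measured.

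The cost is wording only. The schedule already provides the predose and follow-up samples, and no visit, assay or sample-size change is needed.

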**Secondary Objectives:**

- To compare the qualititative (functional) antibody response to pneumococcal vaccination with or without CPG 7909
- To evaluate safety and tolerance of CPG 7909 as a pneumococcal vaccine adjuvant
- To analyze changes in pneumococcal carrier status after pneumococcal vaccination
- To analyze the predictive value of immune activation/status markers such as CD4 count and sCD163 (at the time of vaccination) for the immune response after pneumococcal vaccination.
- To compare antibody responses to pneumococcal vaccination in patients receiving HAART and patients not receiving HAART
- To analyze cellular activity and response before and after vaccination

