**PREDICTORS OF ANTIBODY RESPONSE**

*At baseline.*

- Predictors for vaccine response at six months after 2nd vaccination with Prevenar,

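### Predictors of vaccine response are studied only through high responder yes/no, which costs roughly 12-20 points of power that the continuous IgG data would keep

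*Protocol*

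**What the plan says.** The Protocol's Secondary Objectives include an analysis of "predictive value of immune activation/status markers such as CD4 count and sCD163 (at the time of vaccination) for the immune response after pneumococcal vaccination". The section Predictors of Antibody Response lists "Predictors for vaccine response at six months after 2nd vaccination with Prevenar". Neither names a scale or a threshold.

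Under Statistical Analyses, Secondary endpoints, the outcome becomes binary: "Predictors for achieving a high vaccination response (classified as a high responder) at six months after 2nd vaccination with Prevenar". The model named for it is a Poisson regression with several covariates. The status itself is defined under Primary Endpoints: "Pneumococcal vaccine high responders defined as 2-fold increase and IgG levels ≥1 µg/mL to at least 5 of 7 pneumococcal serotypes".

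The visit is day 270, six months after the second dose at day 90. The Schedule of Assessments has quantitative antibody measurements at baseline and at that visit. The Immunogenicity list already has a continuous endpoint there: "Serotype-specific antibody response defined as change in IgG levels". Linear regression does appear in the analysis section, but only for comparing the arms: "Comparison of endpoints between the study groups will be done by Poisson regression (dichotomous endpoints) or linear regression (continuous endpoints". As written, no predictor analysis uses the antibody level.

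**The concern.** The composite turns seven concentrations, each with its own baseline value, into a single yes/no. A participant who just misses on the fifth serotype counts the same as one who did not respond at all. The named candidate markers are continuous, so a graded relation between marker and response is what one would look for, and the cut discards part of it. For the arm comparison the sample size was built around this binary outcome. Nothing in the predictor objective calls for the same cut.

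What is at stake is how to read a negative result. If CD4 count or sCD163 shows no significant association, the reader cannot tell how far this reflects the marker and how far it reflects an outcome stripped of information that the trial had already collected.

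**Working it through.** **Inputs from the protocol (Estimated Sample Size).** High responders 30% in control and 60% with CPG 7909, two-sided alpha 0.05, power 0.80, 42 per group evaluable, 10% drop-out, 94 enrolled. The protocol gives no power figure for the predictor analysis.

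**The protocol's own figure.** With pooled variance and no continuity correction:

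n = [1.96·√(2·0.45·0.55) + 0.8416·√(0.30·0.70 + 0.60·0.40)]² / 0.30² = (1.379 + 0.565)² / 0.09 ≈ 42 per group.

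42/0.90 = 46.7, so 47 per group and 94 in total. This matches, and all 25 cells of the sample size table reproduce.

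**Expected high responders.** 0.30·42 + 0.60·42 = 12.6 + 25.2 = 37.8 of 84, a pooled rate of 0.45.

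**Analytic size of the loss.** Assume the response behind the cut is normal. Cutting it at a point with proportion p above multiplies its correlation with a marker by φ(z_p)/√(p(1−p)). At p = 0.45 this is 0.3958/0.4975 = 0.796. Its square is 0.633, so the yes/no outcome carries about as much information on the marker as 0.633·84 ≈ 53 participants with the continuous outcome.

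Power by Fisher's z is Φ(atanh(r)·√(n−3) − 1.96). At n = 84 and r = 0.30:
- continuous: 0.3095·9 − 1.96 = 0.826, power 79.6%
- cut, r = 0.30·0.796 = 0.239: 0.2434·9 − 1.96 = 0.230, power 59.1%

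The loss is about 20 points. Over r = 0.20, 0.25, 0.30, 0.35 and 0.40 the analytic losses are 14, 19, 20, 18 and 12 points.

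**Simulation with the planned model.** The latent response is normal within arm, with 30% and 60% above the cut, and the marker has within-arm correlation r to it. Poisson regression of the yes/no outcome on arm and marker is compared with linear regression of the uncut response on the same terms, with 4000 runs per setting. The Poisson model is given a robust variance, so the loss shown comes from the cut and not from the standard error.

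| r | n=84: yes/no | n=84: continuous | loss | n=94: yes/no | n=94: continuous | loss |
|---|---|---|---|---|---|---|
| 0.20 | 32.8% | 44.6% | 11.8 | 34.8% | 48.7% | 13.9 |
| 0.25 | 45.0% | 62.4% | 17.4 | 49.0% | 68.2% | 19.2 |
| 0.30 | 60.7% | 79.5% | 18.8 | 64.9% | 84.7% | 19.8 |
| 0.35 | 73.3% | 90.5% | 17.2 | 78.6% | 93.2% | 14.6 |
| 0.40 | 85.5% | 97.0% | 11.5 | 88.2% | 98.0% | 9.8 |

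With HAART and age added to both models (n = 84), the losses at r = 0.20, 0.30 and 0.40 are 11.8, 19.8 and 12.0 points.

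**Simulation of the composite itself.** The table uses a single latent variable, which nobody observes. When seven serotypes are simulated with the 5-of-7 rule and the continuous outcome is the mean log fold change, the loss is 14-25 points. At r = 0.30, power is 50% against 74% with an assumed serotype correlation of 0.5, and 55% against 77% with 0.7. Against the baseline-adjusted mean log IgG the loss is about 15-29 points. These figures rest on serotype correlations, standard deviations and baseline levels that the protocol does not give.

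**The case against.** The strongest reply is that nothing here is contradictory. The objective leaves the scale open, and the analysis section fills it in with the trial's own definition of response. Asking which markers predict the primary outcome is coherent and gives prevalence ratios on the same scale as the primary analysis. The definition also has a precedent: the Background reports it as the primary endpoint of a French prime-boost trial in HIV patients. It measures breadth across serotypes, whereas a mean log IgG can be raised by a few strongly responding serotypes, so the continuous model asks a somewhat different question. The objective is secondary and carries no power claim, and a later analysis plan could add a continuous model without contradicting the protocol.

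Most of this stands. It is a reason to keep the high-responder model, but not a reason to make it the only predictor analysis, since the objective concerns the response in general and the protocol itself fixes the narrower outcome.

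Several stronger readings are tempting and are not supported:
- A reader might infer that a real moderate predictor would probably be missed. At r = 0.30 to 0.40 the planned analysis has about 61% to 86% power, so such a marker is more likely to be found than missed.
- A reader might infer that about 38 high responders are too few for the model. That depends on how many markers enter, which the protocol does not fix.
- A reader might infer that the continuous IgG data go unused. They are analysed between arms at three visits, and endpoints are also compared by HAART status. What is missing is their use for markers such as CD4 count and sCD163.

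**Conclusion.** The point holds as a moderate loss of efficiency in a secondary analysis. With the protocol's planning figures, restricting the predictor analysis to high responder yes/no costs roughly 12-20 points of power at 84 evaluable participants (about 10-20 if all 94 are evaluable) for a continuous marker with within-arm correlation 0.20-0.40 to the response. The loss is largest around 0.25-0.30.

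At r of about 0.25 or less the planned analysis misses a true predictor more often than it finds it (power 45% at 0.25 and 33% at 0.20). At 0.25 the continuous model reaches 62%, but at 0.20 it also stays below one half (45%). A negative result for CD4 count or sCD163 would therefore be less informative than the data allow, without being worthless.

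The direction is secure. The size is illustrative: the correlations and the normal response behind the cut are assumptions, and the larger losses for the 5-of-7 composite depend on further ones. The primary result is not touched.

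**What to change.** In Statistical Analyses, Secondary endpoints, add a prespecified predictor analysis: linear regression of the day-270 mean of the seven log IgG concentrations on the baseline markers, adjusted for treatment arm, HAART status and baseline mean log IgG, with effects reported as geometric mean ratios. Name it as the more powerful predictor analysis. Keep the high-responder Poisson model alongside it for breadth of response and comparability with the primary endpoint.

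This takes about one sentence of text and one more model on data already collected, with no new samples or visits. The price is a second effect scale to report, and an outcome that measures magnitude rather than breadth, so the two models may not agree and the text should say what each one answers.
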